#### Intervention

The intervention will be based on evidence-based guidelines for the prevention of T2D [23]. These guidelines include a combination of physical activity and dietary intervention and focus on behavior maintenance. Physical activity and diet counseling will be conducted in gender-specific groups by a multidisciplinary team. In order to be easily implemented, the program will be adapted to present resources in primary health care and the community. Figure 1 shows a flow chart summary of the study.

**Figure 1 F1:**
[figure not shown]
Flow chart summary of the 6-month lifestyle intervention study.

Ten group counseling sessions will be provided during a period of 6 months. Each group will contain 16 individuals of the same gender (there will be five groups of men and five groups of women). The sessions target diet, physical activity and behavioral change with the goal of equipping the subjects with the necessary knowledge and skills to gradually achieve permanent behavioral changes. Behavioral change is a model involving *motivation*, *action* and *maintenance*[24]. It supports changes in diet and physical activity and goal-setting, and involves action planning with goals and coping strategies. The intervention group will be supported in their efforts to reach the following goals, which are considered to have preventive effects against diabetes [15,24]: weight reduction of ≥5%, moderate intensity physical activity ≥30 minutes at least 5 days/week, dietary fat <30% of total energy (E%), saturated fat <10 E% and fiber ≥15 g/1000 kcal. The participants will also be encouraged in everyday life to reduce their time spent physically inactive, *e.g.* sitting or lying down, as much as possible. The intervention group will be encouraged to regularly fill in a “smart goal” sheet to help them to specify their goals (such as to lose 0.5 kg per week), and to explain why they want to do it (for example “*I don’t want to get diabetes*”), how they will reach their goals (“*I will walk briskly for 30 minutes every day after work*”) and the coping plan they will apply to conquer different possible obstacles that may appear (“*I will ask my grandmother to come over and babysit while I am away at practice*”), as suggested in the European guidelines to prevent diabetes [24].

#### Group counseling sessions

The participants will have group consultations with the Arabic speaking health coach and/or a nutritionist on preplanned topics, such as how lifestyle affects diabetes and cardiovascular risk, healthy lifestyle habits, goal setting and problem solving, with open discussions focusing on individual problems and behavioral change. In addition, there will be between-visits phone calls to encourage and motivate the participants to maintain their new lifestyle habits.

#### Exercise sessions

Previous studies have shown beneficial effects of aerobic and resistance training on glucose metabolism in subjects with IGT [25,26]. In this study, physical activity will be prescribed using physical activity on prescription (in Swedish “*FaR*” [27]. The participants will be encouraged to participate in a physical activity program combining resistance exercise and endurance training two to three times a week to increase their possibility of reaching outcome goals. The resistance exercise training will be performed with their own body weight, rubber bands and dumbbells and aims to increase muscle strength and endurance. The aerobic endurance training will comprise self-selected activities, such as aerobic classes, swimming, soccer, jogging or walking led by certified instructors. As far as possible, the endurance classes and resistance training classes will be supervised by a leader from Iraq of the same gender as the group. Participation lists will be filled in by the supervisors of the physical activity classes.

#### Assessment and outcome measures

Trained Swedish- and Arabic-speaking research nurses will conduct the measurement procedures. Measurement will be conducted at baseline, in the middle of intervention (3 months) and at the end of intervention (6 months). Table 1 shows a schedule for the assessments that the participants will undergo during the study period.

**Table 1 T1:** Schedule of assessments and assessment measures

	**Screening**	**Baseline**	**Months**	
			**3**	**6**
**Anthropometrical**				
Height	x	x		
Weight	x	x	x	x
Waist circumference	x	x	x	x
Buttock circumference	x	x	x	x
**Clinical**				
Fasting plasma glucose	x	x	x	x
Cholesterol	x	x	x	x
Triglycerides	x	x	x	x
HDL-C	x	x	x	x
LDL-C	x	x	x	x
HbA1c	x	x	x	x
C-peptide	x	x	x	x
s-insulin	x	x	x	x
OGTT	x	x	x	x
**Physical cctivity**				
IPAQ		x	x	x
ActiGraph	x	x	x	x
VO_2_ max		x	x	x
**Dietary**				
Food record		x	x	x
**Physical and mental wellbeing**				
EQ-5D		x	x	x
Hospital Anxiety and Depression Scale	x	x	x	x
(HADS)				
**Questionnaire**				
Sociodemographics	x	x		
Stage of change		x	x	x
Self-determination theory (TSRQ)		x	x	x
Alcohol habits (AUDIT)	x	x	x	x
Tobacco habits	x	x	x	x
Cost				x
Willingness to pay (WTP)				x

#### Sociodemographic measurements

Sociodemographic data will be collected at baseline only and will include age, education level, household income, employment status, marital status, years spent in Sweden, language spoken at home and with friends, complete family history of diabetes in first- and second-degree relatives, current and previous illness and co-morbidities, and current medications.

#### Anthropometrical measurements

Height will be measured to the nearest centimetre using a wall-mounted stadiometer. Weight will be measured to the nearest kilogram with participants wearing light clothing, but not shoes, using a calibrated 34–5062 RTC3010 electronic scale (Coline, China). Body mass index (BMI) will be calculated as weight (kg) divided by height squared (m^2^). Waist circumference will be measured twice with a tape to the nearest 0.1 cm at the midpoint between the lowest rib margin and the iliac crest. Buttock (hip) circumference will be measured where the protrusion of the buttocks is greatest.

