**Methods/design:**

In this randomized controlled trial, 308 participants (born in Iraq, living in Malmö, Sweden and at high risk of type 2 diabetes) will be allocated to either a culturally adapted intervention or a control group. The intervention will consist of 10 group counseling sessions focusing on diet, physical activity and behavioral change over 6 months, and the offer of exercise sessions. Cultural adaptation includes gender-specific exercise sessions, and counseling by a health coach community member. The control group will receive the information about healthy lifestyle habits provided by the primary health care center. The primary outcome is change in fasting glucose level. Secondary outcomes are changes in body mass index, insulin sensitivity, physical activity, food habits and health-related quality of life. Measurements will be taken at baseline, after 3 and 6 months. Data will be analyzed by the intention-to-treat approach. The cost-effectiveness during the trial period and over the longer term will be assessed by simulation modeling from patient, health care and societal perspectives.

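### Recording weight to the nearest kilogram adds a small rounding error to change in weight and BMI, which is avoidable if the scale displays finer steps

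*Protocol article*

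**What the plan says.** The protocol article fixes the measurement rule under Anthropometrical measurements: "Weight will be measured to the nearest kilogram with participants wearing light clothing". The instrument is a named, calibrated electronic scale whose display step is not given. In the same paragraph, "Height will be measured to the nearest centimetre using a wall-mounted stadiometer", and waist is taken twice to 0.1 cm. BMI follows from the first two: "Body mass index (BMI) will be calculated as weight (kg) divided by height squared".

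Weight enters the analysis in several places:

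- The abstract lists the secondary outcomes: "Secondary outcomes are changes in body mass index, insulin sensitivity, physical activity, food habits and health-related quality of life".
- Univariate and multivariate analysis names weight among the effects to be compared between arms.
- Follow up and evaluation of data has BMI followed every 3 months.
- Economic evaluation uses BMI as one of the outcomes extrapolated in the long-term model.

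The primary outcome does not involve weight: "The primary outcome is change in fasting glucose level".

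**The concern.** An electronic scale often shows a finer reading than a whole kilogram. If this one does, the rule discards information at each visit, and the article gives no reason for doing so. The loss falls on change scores, where two rounded readings are subtracted and both rounding errors remain in the result. The waist measurement in the same paragraph is held to a much finer step. What is at stake is some precision in the weight and BMI comparisons and in the BMI input to the long-term model.

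**Working it through.** The article gives no SD, target difference or power for weight or BMI, so there is no stated figure to reproduce.

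**Inputs from the article:** recording step 1 kg (Anthropometrical measurements); 130 completers per group, 260 in all (Eligibility criteria).

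**Assumptions, not in the article:** SD of weight change 3 to 6 kg, with 2 kg as an extreme; height 1.60 to 1.75 m; two-sided 5% test. Rounding is treated as a uniform error, independent at each visit, which is reasonable when weights vary over many kilograms.

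**Step 1, rounding error in kilograms.** Each reading is off by at most 0.5 kg, with SD 1/√12 = 0.289 kg. For a change between two readings, the SD is √(2/12) = 0.408 kg.

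**Step 2, in BMI units.** Divide by height squared: 0.408/1.75² = 0.133 kg/m² and 0.408/1.60² = 0.159 kg/m².

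**Step 3, variance and power.** The variance of change rises by the fraction (1/6)/SD². The participants needed to offset this are 260 times that fraction. For power, take the difference that has 80% power without rounding, d = SD × (1.960 + 0.842) × √(2/130), and recompute with SD′ = √(SD² + 1/6).

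| Assumed SD of change (kg) | Variance inflation | Equivalent participants (of 260) | Power, from 80.0% |
|---|---|---|---|
| 2 (extreme) | 4.2% | 10.8 | 78.4% |
| 3 | 1.9% | 4.8 | 79.3% |
| 4 | 1.0% | 2.7 | 79.6% |
| 5 | 0.7% | 1.7 | 79.7% |
| 6 | 0.5% | 1.2 | 79.8% |

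**Step 4, bias.** The same rule applies in both arms. Rounding to the nearest unit is as likely to raise a reading as to lower it, so the difference in mean change is essentially unbiased.

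**Step 5, after the change.** With a 0.1 kg step, the rounding SD of a change is 0.1 × 0.408 = 0.041 kg. At an SD of change of 3 kg, the variance inflation is (0.01/6)/9 = 0.02%.

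**Step 6, comparison with height.** For a person of 1.65 m and 80 kg, height rounding of 0.5 cm moves the BMI level by about 0.18 kg/m², much as weight rounding of 0.5 kg does. For change in BMI the two differ. Table 1 schedules height at screening and baseline only. If the baseline height is used throughout, its error is shared by all visits and only rescales the change, by (1.65/1.645)² − 1 = 0.6%. Weight rounding enters anew at each visit.

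**The case against.** The strongest case against is that this is a measurement preference and not a fault. Nothing in the rule is wrong or contradictory. A variance increase of 1% to 2% on a secondary outcome with no power target would change no conclusion. Weights are taken in light clothing with no stated correction, so some of the extra digits would be noise. The scale may also display only whole kilograms. The point about size stands in full, and the point about the scale makes the gain conditional. Neither gives a reason to discard a finer reading where one is available.

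Three stronger readings are tempting, and the article does not support them.

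- **Misclassification of the weight goal.** A reader might infer that rounding misclassifies people on the goal of "weight reduction of ≥5" per cent. Under Intervention, that figure is one of several goals which the intervention group is helped to reach. The article does not make it an outcome, a responder definition or an eligibility rule, and controls are given no percentage. Were someone to classify by it, simulation under assumed mean weights of 75 to 90 kg, mean changes of 0 to −4 kg and SDs of change of 2.5 to 5 kg has about 1.5% to 4.0% of individuals changing side. The errors run both ways and nearly cancel: in one scenario the true proportion is 25.8% and the recorded one 26.2%.
- **Conflict with the example goal of losing 0.5 kg per week.** That is an illustrative entry for a participant's own goal sheet. Trial weights are taken at baseline, 3 and 6 months, and 12 weeks at that rate would be 6 kg, well above the rounding step.
- **Avoidable as a fact.** This depends on the display step, which is not stated.

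**Conclusion.** The point holds as a minor improvement. The stated rule adds a rounding error with SD 0.41 kg to each change in weight, which feeds a planned weight analysis and the BMI secondary outcome. For an assumed SD of change of 3 to 6 kg, power falls by 0.7 to 0.2 points from 80%; even at an extreme 2 kg it falls by only 1.6 points. Fasting glucose and its power calculation are unaffected. These sizes rest on SDs that the article does not give, and whether the loss can be avoided rests on the scale displaying finer than 1 kg.

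**What to change.** Under Anthropometrical measurements, have weight recorded at every visit to 0.1 kg, or to the scale's display step if that is coarser, and compute BMI from the recorded value without further rounding. State the display step of the scale. If the scale shows finer than 1 kg, this costs one change of wording and no extra measurement. If it shows whole kilograms only, the present rule can stand and the point lapses. Trial status gives recruitment from October 2013, so under the article's own timetable the change could precede the first trial weights. Apply the same step in both arms and at all three visits.

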#### Biomedical measurement

Participants will be instructed not to eat or drink anything but water or consume tobacco after 10 pm the day before testing and to bring a record of their current medications. Blood pressure will be measured in the supine position after five minutes’ rest and with the arm at heart level. The mean of two measurements, taken one minute apart, will be used in analyses. Blood samples will be collected in the morning and analyzed continuously during the study. Serum insulin (s-insulin) levels will be measured by Access^©^ Ultrasensitive Insulin radioimmunoassay (Beckman Coulter, USA) [28]; serum cholesterol and triglyceride levels will be measured using enzymatic methods (Bayer Diagnostics) [29]. Serum HDL-cholesterol levels will be measured enzymatically after isolation of LDL and VLDL (Boehringer Mannheim GmbH, Germany); LDL-cholesterol levels will be estimated using Friedewald’s equation [30]. C-peptide levels will be measured with a one-step immunometric sandwich electrochemiluminescence immunoassay (ECLI) based on a ruthenium (Ru) derivative (Roche). A standard 75-g OGTT will be performed and blood samples will be collected at 0, 30, 60 and 120 min. Blood glucose (f-glucose) will be measured in venous whole blood immediately after sampling using a photometer (HemoCue AB, Ängelholm, Sweden) [31]. HbA1c will be estimated by high-pressure liquid chromatography (HPLC) with a VARIANT™ TURBO Hemoglobin A1c Kit 2.0 (Bio-Rad). ISI, corrected insulin response (CIR) and DIo will be calculated from the OGTT results. ISI will be calculated as follows:

$$\begin{array}{ll} \mathrm{ISI}= & 10,000/\surd [\left(f-\mathrm{glucose}\;\left(\mathrm{mmol}/L\right)\times s-\mathrm{insulin}\;\left(\mathrm{mIE}/L\right)\right)\;\\ & \times \left(\mathrm{mean}\;\mathrm{OGTT}\;\mathrm{glucose}\;\mathrm{conc}.\left(\mathrm{mmol}/L\right)\right)\\ & \left(\times \mathrm{mean}\;\mathrm{OGTT}\;\mathrm{insulin}\;\mathrm{conc}.\left(\mathrm{mIE}/L\right)\right)]\; \end{array}$$

[32].

CIR provides an estimation of beta-cell function and will be calculated as follows:

$$\mathrm{CIR}=(100\times \mathrm{insulin}\;\mathrm{at}\;30\;\min/\left(\mathrm{gluc}30\times \left(\mathrm{gluc}30–3.89\right)\right)$$

[33], where gluc30 is glucose at 30 min and must be >4.44 mmol/l and >f-glc [34].

DIo provides an estimate of beta-cell function adjusted for insulin resistance, and is calculated as CIR multiplied by ISI [35].

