#### Intervention group

The intervention group will be offered (A) regular group sessions led by an Arabic-speaking health coach with a similar ethnic background to the group and (B) free physical activity sessions. Others showed that the willingness to enroll in a diabetes prevention program was predicted by perceived risk of diabetes [22] and before the start of the study we will hold an education session to provided information about how our lifestyle habits influence our health.

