#### Control group

Information will be sent to the primary health care center (PHCC) that the participant is at high risk of T2D and that he/she will participate in the study as control. The control group will receive “treatment as usual”, *i.e.* they will be instructed by nurses in the PHCC to increase their physical activity, to reduce their weight and to make the same diet changes as those recommended to the intervention group.

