#### Physical activity and cardiorespiratory fitness

We will use two types of physical activity measurement methods: self-report and objective. The self-administered, long version of the International Physical activity Questionnaire (IPAQ) will be used to assess self-reported physical activity level, as it may provide the most reliable data for the present study [36]. IPAQ is one of the most used and evaluated questionnaires [36]. However, self-report methods may be subject to recall bias and may provide different results compared to objective instruments such as accelerometers [37]. Therefore, we will also use ActiGraph accelerometers, which are most commonly used in research to provide an objective measure of duration, intensity and frequency of physical activity. Physical activity during all waking hours in a 10-day period will be measured every second month with ActiGraph GT3X accelerometers (Pensacola, Florida, USA). The GT3X accelerometer provides sufficient storage capacity for the measurement period, shows high intra- and inter-monitor reliability [38,39] and may capture a wide range of physical activity intensities [40,41]. A period of 10 days provides sufficient information to capture the variation in physical activity [42].

Cardiorespiratory fitness will be assessed by measuring maximum aerobic capacity (VO_2_ max). Subjects will undergo a 6-minute walking test that provides an indirect estimate of oxygen uptake [43] and that has been validated in subjects up to 65 years of age [44]. Performance is estimated by measuring heart rate and walking time at the end of the test, with adjustment for age, gender and BMI. A prerequisite for conducting the test is the ability to walk briskly and to achieve a heart rate of ≥70% of the age-related maximal heart rate.

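### The pre-test rule covers food, drink and tobacco but not exercise, so closeness of an exercise class to blood sampling can differ by arm at follow-up and shift mean ISI modestly

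*Protocol article*

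**What the plan says.** Biomedical measurement sets out how participants prepare for testing: "Participants will be instructed not to eat or drink anything but water or consume tobacco after 10 pm the day before testing". They also bring a record of their medicines. On timing it says: "Blood samples will be collected in the morning and analyzed continuously during the study". ISI, the corrected insulin response (CIR) and the oral disposition index (DIo, which is CIR times ISI) all come from the OGTT. No section limits exercise before a test, spaces visits from exercise classes, or asks when the participant last exercised.

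Under Exercise sessions, intervention participants are "encouraged to participate in a physical activity program combining resistance exercise and endurance training two to three times a week". Their wider goal, in the Intervention section, is "moderate intensity physical activity ≥30 minutes at least 5 days/week". Controls have no programme classes, but "they will be instructed by nurses in the PHCC to increase their physical activity" (Control group). Table 1 places blood tests at baseline, 3 months and 6 months, so the follow-up tests fall during and at the end of the programme. Table 1 marks an OGTT at 3 months as well, whereas Follow up and evaluation of data names it only for the final evaluation; the point applies at 6 months either way.

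The Abstract lists insulin sensitivity as a secondary outcome. Aim 2 and Follow up and evaluation of data ask whether the change in fasting glucose depends on ISI, DIo or family history.

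**The concern.** The preparation rule is specific, down to the hour and to tobacco, yet it omits a pre-test behaviour that the trial sets out to change. The omission would matter little if recent exercise were equally common in both arms at every visit. It need not be: programme classes exist in one arm only, and only after baseline. Randomisation balances the arms before the programme starts, and subtracting baseline removes only what was present then. Neither removes an imbalance in recent classes that arises at follow-up.

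If a single bout raises insulin sensitivity for about a day (general physiology, taken here as an assumption), follow-up ISI in the intervention arm mixes a short-lived response with lasting change. The analysis that uses ISI and DIo to explain the glucose change inherits the mixture. So does the analysis that relates these changes to the amount of activity, because frequent attenders are the most likely to be tested soon after a class.

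**Working it through.** The plan states no figure on this point, so there is none to reproduce.

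**Inputs.**
- Classes per week, s: 2 to 3 (Exercise sessions).
- Sampling in the morning (Biomedical measurement), so a class on the previous afternoon or evening is less than 24 hours earlier.
- Share of classes attended, a: not given. Assumed range 25% to 100%.
- Relative rise in ISI about a day after a bout, b: not given. Assumed range 10% to 20%.
- Test day unrelated to class days: assumed, since no scheduling rule is stated.

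**Share tested the day after an attended class: a × s/7.**

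| Attendance | 2 per week | 3 per week |
|---|---|---|
| 100% | 2/7 = 29% | 3/7 = 43% |
| 75% | 21% | 32% |
| 50% | 14% | 21% |
| 25% | 7% | 11% |

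From programme classes, the share is 0% in controls, and 0% in both arms at baseline. These zeros count classes, not all exercise.

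**Two-day window, full attendance.** Averaged over all layouts of class days in a week, the share is 1 − C(5,s)/C(7,s): 1 − 10/21 = 52% for two classes and 1 − 10/35 = 71% for three. Particular layouts range from 43% to 86%.

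**If the activity goal is just met.** The day before a test is an active day in 5/7 = 71% of cases.

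**Shift in the intervention arm's mean ISI: share × b.**
- Full attendance: 0.286 × 10% = 2.9% to 0.429 × 20% = 8.6%.
- 50% attendance: 0.143 × 10% = 1.4% to 0.214 × 20% = 4.3%.
- 25% attendance: 0.071 × 10% = 0.7% to 0.107 × 20% = 2.1%.

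**What b implies.** ISI is proportional to one over the square root of fasting glucose × fasting insulin × mean glucose × mean insulin. With glucose unchanged, a rise of 10% to 20% corresponds to fasting and mean insulin both lower by 9% to 17% (1/1.10 = 0.909; 1/1.20 = 0.833).

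**DIo.** Because DIo is CIR × ISI, a shift in ISI passes through in proportion if CIR is unchanged. CIR uses insulin and glucose at 30 minutes, which may also move, so the net shift in DIo is not determined.

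**The case against.** Several objections have force.

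- *A condensed article may leave visit procedures to a fuller protocol.* That is possible. But the article spells out its preparation rule, so adding exercise to it is a fair request.
- *The mechanism and its size are not in the documents.* This is true, and so the result is a range under stated assumptions. Attendance is also unknown: classes are offered, not required, and at 25% attendance the shift is about 2% at most.
- *Testing on an ordinary day reflects the assigned lifestyle.* This is a reasonable view of what to estimate. However, the counselling aims at permanent change in behaviour, and the plan uses ISI and DIo to explain the glucose effect. With the time of the last bout neither controlled nor recorded, short-lived and lasting change cannot be reliably separated.
- *Recent activity is partly recoverable.* Class lists are kept, and accelerometers are scheduled at follow-up. The lists cover classes only, however, and the article does not tie the accelerometer period to the blood test.

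A reader might also infer more than the documents support:

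- That controls do not exercise. They are told to be more active; only the contrast in programme classes is firm.
- That the between-arm difference in ISI is inflated by 3% to 9%. That figure is a shift in one arm's mean; the documents give no expected ISI difference to scale it against.
- That the walking test biases the comparison. It requires participants "to achieve a heart rate of ≥70% of the age-related maximal heart rate", but Table 1 schedules it for both arms at the same visits. If done before sampling it adds noise to both arms alike, and no order or shared day is stated.
- That the shift reaches the long-term model. Economic evaluation builds that model on BMI, blood pressure and lipids, not ISI.

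**Conclusion.** The gap is real and modest. The preparation rule omits exercise, and exposure to recent programme classes differs by arm and visit in a way that neither randomisation nor change from baseline removes. Under an assumed acute rise of 10% to 20%, mean ISI in the intervention arm at follow-up shifts by about 3% to 9% at full attendance and about 1.4% to 4% at 50%. Exercise by controls on nurse advice would narrow the contrast between arms by an unknown amount. The consequence is confined to ISI, a secondary outcome, and to analyses that use ISI or DIo. Whether fasting glucose, the primary outcome, is affected is uncertain, and the documents do not support calling the primary result biased. This is a worthwhile low-cost improvement.

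**What to change.** Add to the participant instructions in Biomedical measurement, for both arms and every visit including baseline: no exercise class or other strenuous exercise in the 24 hours before blood sampling, with ordinary walking allowed. Add one form field for the time of the last bout, so that a sensitivity analysis of ISI and DIo can use it together with the participation lists. As a minor point on noise, do any same-day walking test after the 120-minute sample.

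The cost is one line of instruction, one form field and at most one rescheduled class per visit. The rule removes only part of the effect, because ordinary walking continues and walking is itself among the programme's activities. The recorded time of the last bout is therefore needed as well.
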